### Participants

Inclusion criteria for *perinatal intervention participants* include (1) 16 years of age or greater; (2) Identify as Latina; (3) Speaks Spanish/prefers to receive services in Spanish; (4) Pregnant or have a child 9 months or younger; At risk for a major depressive episode based on the following: mild to moderate depressive symptoms [5–14] on the Edinburgh Postnatal Depression Scale [52] and/or presence of risk factors for Major Depressive Episode (MDE) onset as measured by the Postpartum Depression Predictors Index-Revised (PDPI-R) [53–55]; ≥ 3 on PDPI-R when administered prenatally or ≥ 4 on the PDPI-R postnatally, or history of depression as indicated on the PDPI-R, regardless of score). Study exclusion criteria include (1) Individuals who score > 14 on the EPDS (likely meet criteria for a current major depressive episode for whom treatment would be recommended (vs. preventive intervention for depression); (2) Individuals who are not at risk for PPD—i.e., scores < 5 on the EPDS and under the aforementioned cutoffs on the PDPI-R and no personal history of depression; (3) Staff concern about cognitive limitations of a potential participant such that there is concern that they would not understand the intervention material; (4) Staff concern about a potential participant’s capacity to engage in a group intervention (e.g., concern about disruptive behavior); and (5) Unable to speak and understand Spanish.

As part of exploratory analyses, we will recruit *children of perinatal study participants* who are between the ages of 2.5 and 4.5 years at baseline. Inclusion criteria for intervention facilitators/staff and Judy Center directors include that the staff is a facilitator or co-facilitator of MB-VG groups or a director at a site participating in the study (either referring participants or delivering via their site). We plan to enroll a total of 486 study participants: (1) 300 perinatal individuals, (2) 150 children of perinatal individuals, (3) 24 MB-VG facilitators, and (4) 12 Judy Center directors.

### Recruitment and consent

Recruitment will take place at participating Maryland Judy Centers. Planned recruitment strategies will include (a) flyers posted at Judy Center sites and (b) referrals from Judy Center staff. We anticipate most perinatal individuals will be recruited via referrals from Judy Center staff. The study team will work with each site to review eligibility criteria prior to recruitment. For women who are referred by staff and express interest, research staff will reach out by phone to discuss study procedures and administer a telephone screening, including the EPDS and PDPI-R. Individuals scoring 5–14 on the EPDS and/or ≥ 3/4 on the PDPI-R will be eligible for the study. Eligible participants will be able to consent either over the phone/zoom via oral consent, or independently through a unique electronic link sent by Research Electronic Data Capture (REDCap) [56], with research staff notifying participants as to their study arm assignment. Internet hotspots will be available for participants who would need them, and we budgeted a data plan stipend for all study participants, to offset costs related to study participation Fig. 1.

**Fig. 1 Fig1:**
[figure not shown]
Schedule of screening, enrollment, interventions, and assessments

We anticipate that approximately 24 Judy Center staff will serve as MB-VG facilitators during this study. Each Judy Center staff member who facilitates a MB-VG cohort will be asked to provide informed consent prior to the first group they facilitate. A REDCap link with the informed consent form will be sent to and e-signed by the Judy Center staff/facilitator prior to facilitation. We will recruit the director from each of the 12 participating Judy Centers. Each director will be asked to provide informed consent prior to the completion of the baseline survey and prior to MB-VG implementation at their agency. The informed consent will be sent electronically via a REDCap link.

### Study intervention

#### MB-VG

Women randomized to the MB-VG arm will begin to receive the 10-session MB-VG intervention within 1 month of enrollment. These sessions are delivered weekly over a maximum of 15 weeks, with each session lasting between 60 and 75 min. All MB-VG groups will be delivered in Spanish by a trained MB-VG facilitator. Prior to each session, a member of the research team will test Zoom connections with each participant. Each session consists of cognitive-behavioral therapy-based content and is comprised of didactic and interactive content and ends with a “personal project” that encourages clients to practice using the core skills they learned in the session (see Table 1 below for core content found in each MB-VG session). In addition, a pediatrician will provide content related to nutrition, parenting, and child development. Text messages will be used as an implementation strategy to promote session attendance, encourage skill practice, and reinforce pediatrician content. Two bilingual Judy Center staff will co-facilitate each MB-VG intervention cohort. Based on previous MB research, attendance at over 50% of intervention sessions is defined as “full-dosage”; therefore, for this study, receipt of ≥ 6 sessions will constitute full-dose of MB-VG. We will document attendance at intervention sessions by asking one of the intervention co-facilitators to complete an attendance log for each MB-VG session. A member of the research team will also use Zoom login information to confirm the information found in the attendance logs. Participants who do not attend a session will receive a brief link via text to a video that reviews the session topics and key points. All videos for missed session are approximately 5 min or less.

#### Usual care

Women randomized to the usual family support services/usual care arm will receive Judy Center services without any MB-VG intervention during the study period (but will receive MB-VG after 6 months via our delayed intervention design, if interested). Judy Centers provide an array of services including parenting education, case management, family health and developmental assessments and referrals, and partnerships with childcare and education providers (e.g., Head Start).

### Training and supervision of MB-VG facilitators

All participating Judy Centers have been on MB-VG, or will be trained prior to beginning facilitation. Trainings provide six contact hours on:Conceptual underpinnings of MB-VG (e.g., cognitive-behavioral therapy, psychoeducation, and attachment theories)Format of the MB-VG instructor manual; specifically, for each new concept the manual presents: (a) key points, (b) rationale for concept, (c) considerations for facilitators, including sensitive issues that may emerge, and (d) a step-by-step script for introducing material.Facilitation of virtual groups. For example, strategies for encouraging participation of more introverted group members and troubleshooting common technology issues.Review of core CBT and attachment content in each MB-VG session. Each session is discussed from start to finish and various techniques are used to review MB-VG content (e.g., role plays, small group activities, structured discussion questions) to allow for multiple learning styles.Importance of addressing food insecurity and parenting/child development and details on how the pediatrician is integrated into MB-VG delivery and procedures for referral to assistance with nutrition assistance program enrollment.Overview of implementation protocol which includes information about (1) recruitment and referral processes, (2) preparing for virtual groups, (3) MB-VG session implementation (during and post sessions), (4) connecting participants to a resource advocate (FindHelp), (5) using HealthySMS for text messages, and (6) technology considerations.

Prior to delivering their first MB-VG cohort, staff who were initially trained > 6 months before study start will receive a 2-h refresher and protocol training via Zoom. This training will debrief facilitators’ prior experiences, if any, delivering MB-VG and discuss the study protocol and implementation logistics. Consistent with prior MB trials, while delivering their first MB-VG cohort, a facilitator will receive weekly supervision by research team members with expertise in the intervention. Within 1–2 weeks before implementation of the first group session the facilitator and co-facilitator(s) attend a 45–60-min virtual training to review the implementation protocol and technology considerations and needs.

Centers participating in the study that do not have bilingual staff (or do not have sufficient bilingual staff) will be able to refer participants to sites with trained bilingual staff, a key benefit of the virtual modality. To enhance the pragmatic nature of the study, staff with varied disciplinary backgrounds (e.g., child development, social work) will all be eligible to facilitate MB-VG virtual groups.

### Measures: Perinatal Latinas

Related to our effectiveness aims, we will collect data from perinatal individuals and their children. Each data collection procedure is listed below, and we will provide additional details on measures and time points in Table 2 below and in the SPIRIT flow diagram. Implementation outcome assessments are described in Table 3 below and guided by the Reach, Effectiveness, Adoption, Implementation, and Maintenance (RE-AIM) framework [48].

**Table 2 Tab2:** Overview of measures and methods to assess intervention effectiveness with perinatal individuals and their children

Effectiveness outcome indicator	Measure(s)	Maternal self-report surveys	Observations	Structured clinical interview
**Baseline Measures**				
Demographic Survey	Developed by investigators	X		
Comfort with Technology	Adapted from Digital Health Care Literacy Scale [57]	X		
**Primary Outcomes**				
Depressive Symptoms	Center for Epidemiologic Studies Depression Scale (CES-D) [58]	X^**1**^		
Depressive Episodes	Structured Clinical Interview for DSM-V- Disorders Research Version (SCID-5-RV) [59]			X^**3**^
Parenting Self-Efficacy & Responsiveness	Parental Cognition and Conduct Towards the Infant Scale (PACOTIS) Parenting Self-Efficacy subscale [60]	X^**3**^		
Parenting Responsiveness	Maternal Infant Responsiveness Instrument (MIRI) [61]; Parenting Clinical Observation Schedule (PCOS) [62]	X^**3**^	X^**2**^	
**Exploratory Child Outcomes**				
Dysregulation	Disruptive Behavior Diagnostic Observation Scale (DB-DOS) [63, 64]		X^**2**^	
School readiness	Bracken School Readiness Composite (BSRC) [65, 66]		X^**2**^	
**Secondary Outcomes and Intervention Mechanisms**				
Behavioral activation	Behavioral Activation Depression Scale (BADS) [67, 68]	X^**1**^		
Decentering	Experiences Questionnaire [69]	X^**1**^		
Social support	Multidimensional Scale of Perceived Social Support (MSPSS) [70]	X^**1**^		
Mood management	Patient-Reported Outcomes Measurement Information System (PROMIS) Self-Efficacy Managing Emotions [71]	X^**1**^		
Anxiety Symptoms	Generalized Anxiety Disorder 7-item (GAD-7) [72]	X^**1**^		
Perceived Stress	Perceived Stress Scale—10-item (PSS-10) [73, 74]	X^**1**^		
Food Insecurity	Household Food Security Scale-Short Form [75]	X^**1**^		
Mental Health Treatment Stigma	Stigma Concerns about Mental Health Care [76]	X^1^		

^1^ Data collected at baseline, 1-wk. Post-intervention., 3 mos. Post-intervention., 6 mos. Post-intervention; ^2^ Data collected at 6 mos. Post-intervention; ^3^ Data collected at 3- and 6-mos. Post-intervention

**Table 3 Tab3:** Overview of measures and methods to assess implementation outcomes

Implementation outcome indicator (Aim 2)	Measure(s)/metrics	Survey timing (respondents)	Sample explanatory/interview questions (Aim 3)	Interview timing (respondents)
**Reach**	% meeting eligibility criteria who enroll	Administrative/Ongoing	What explains barriers to enrollment?	Post-cohort implementation (facilitators) Post-completion of all intervention cohorts at early learning center (directors)
**Effectiveness**	See Table 2		What explains variability in effectiveness?	Post-completion of all intervention cohorts at early learning center (facilitators and directors)
**Adoption**	% sites & facilitators who begin MB-VG	Administrative/Ongoing	Barriers to center & facilitator adoption of MB-VG?	Post-completion of all intervention cohorts at early learning center (directors)
**Implementation**				
Implementation Readiness	Organizational readiness for implementing change [77]	Baseline (facilitators and directors)		
Acceptability	Acceptability of Intervention Measure (AIM) [78, 79] Attendance	Baseline (facilitators and directors) Post-cohort implementation (clients and facilitators) Post-completion of all intervention cohorts at early learning center (facilitators and directors)	Participant, facilitator, community, & site characteristics that explain variability in acceptability, feasibility, appropriateness? Rationale for MB-VG adaptations?	Post-cohort implementation (clients and facilitators) Post-completion of all intervention cohorts at early learning center (facilitators and directors)
Feasibility	Feasibility of Intervention Measure (FIM) [79] Attendance			
Appropriateness	Intervention Appropriateness Measure (IAM) [79]			
Fidelity/ Adaptation	Revised Cognitive Therapy Rating Scale (CTS-R) [80] Modified Adaptation Checklist (MAC) [81, 82]	Post-cohort implementation (facilitators) Post-completion of all intervention cohorts at early learning center (facilitators)		
Cost	Activity-Based Costing [83]	Baseline (facilitators and directors) Post-cohort implementation (clients, facilitators)	How did cost affect MB-VG engagement?	
Maintenance	Sustainment Measurement System Scale (SMSS) [84]	Post-completion of all intervention cohorts at early learning center (directors)	Barriers to maintenance?	

Legend. *C *Client, *F* Facilitator, *D* Director of Judy Center

### Self-report surveys

All participants will be asked to complete surveys at four time points: baseline (pre-intervention), 1-week post-intervention, 3 months post-intervention, and 6 months post-intervention to assess primary and secondary outcomes, as well as acceptability and feasibility. Data will be collected online and managed via REDCap. To minimize potential literacy issues, we will use REDCap’s text-to-speech function to allow participants to listen to audio survey questions if they prefer. For participants who strongly prefer to have a research team member administer surveys, a bilingual research assistant will conduct surveys by phone. We anticipate each survey will take 40–60 min, with participants remunerated $25–40 per survey, depending on the time point.

### Structured clinical interviews

To assess onset of major depression, all participants will be asked to complete the Mood Disorders module of the Structured Clinical Interview for DSM-V Diagnosis, Research version (SCID-5-RV) [85], a semi-structured interview for DSM-V Axis I diagnoses. The SCID will be administered at the 3- and 6-month post-intervention time points. Participants will be compensated $25 for completing the clinical interview at 3-month, and $30 for completing a clinical interview at 6-month post-intervention.

### Virtual observations

Related to our exploratory aim, participants with a child aged 2 ½–4 ½ will be invited to complete a virtual Zoom observation at the 6-month post-intervention time point after they complete their SCID. Observations will be video recorded to facilitate coding, with coded data entered into REDCap for analysis. Based on 2020 Judy Center data, we anticipate ~ 50% of families (*n* = 150) will have a child aged 2 ½–4 ½, who will provide data for this exploratory aim. Participants who complete virtual observations will be compensated $20.

### Qualitative interviews

We will recruit a stratified purposive sample (i.e., sampling from each participating Judy Center, selecting for variability in implementation and effectiveness outcomes) of up to 60 perinatal intervention participants for a semi-structured interview to further explain outcomes (e.g., variability in effectiveness or satisfaction), stopping if we reach data saturation (e.g., no significant new data after several interviews) earlier. Participants who complete qualitative interviews will be compensated $25.

### Measures: MB-VG Facilitators and Center Directors

All MB-VG facilitators (anticipated *n* = 24) will complete a baseline self-report survey through REDCap which includes demographic and pre-implementation questions assessing readiness, feasibility, acceptability, and appropriateness of the intervention as well as anticipated barriers. Additionally, each facilitator will be asked to complete a self-report survey after each MB-VG cohort they facilitate assessing implementation outcomes assessing feasibility, acceptability, and appropriateness of the intervention as well as implementation barriers, with a final implementation survey within 1 month after once all study cohorts are completed at that site. All MB-VG facilitators (*n* = 24) will complete a semi-structured interview after they complete their first MB-VG cohort and within 1 month after MB-VG study implementation is completed at that site.

### Fidelity assessment of intervention groups

All MB-VG sessions will take place via Zoom, with audio of each session transcribed in Spanish using Zoom’s transcription setting, and then uploaded to a secure online folder accessible only to research staff. Each session will be reviewed to document participant attendance and session length, with a random sample of 20% reviewed in depth to assess fidelity. Fidelity will be assessed using the Revised Cognitive Therapy Rating Scale (CTS-R) [80], previously modified to align with MB. Independent raters will assess fidelity by reviewing audio recordings of intervention sessions and documenting on a 3-point scale the extent to which each topic in a MB-VG session was covered. Adaptations will be assessed by asking facilitators to complete the Modified Adaptation Checklist (MAC) [81, 82] after each cohort they lead; the MAC will assess adaptation in 14 different ways (e.g., skipped topics, modified activities) and for each adaptation reported, whether the adaptation was planned. Adaptations will be explored in semi-structured interviews with facilitators and surveys, guided by Framework for Modification and Adaptations [86],

All Judy Center directors (*n* = 12) will be asked to complete a baseline REDCap survey to assess potential barriers to MB-VG implementation and includes demographic and additional pre-implementation questions assessing readiness, feasibility, acceptability, and appropriateness of the intervention as well as anticipated barriers, as well as a final implementation survey within 1 month after all study cohorts at that site are completed. The final survey will assess director perception of feasibility, acceptability, appropriateness of the intervention, and implementation barriers as well as anticipated barriers to sustainment. All Judy Center directors (*n* = 12) will also complete a semi-structured interview after MB-VG implementation is completed.

### Blinding

Because of the nature of the intervention, we will not be able to blind study participants, facilitators, and RAs assisting with the intervention. However, research staff who will be administering the Center for Epidemiologic Studies Depression Scale (CES-D), Parental Cognition and Conduct Towards the Infant Scale (PACOTIS) Parenting Self-Efficacy subscale, Maternal Infant Responsiveness Instrument (MIRI), SCID assessment, Disruptive Behavior Diagnostic Observation Scale and Bracken Basic Concept Scale School Readiness Composite will be blinded to study condition. Research staff who will be coding the DB-DOS and Bracken Basic Concept Scale School Readiness Component will also be blinded to study condition.

### Statistical analysis

Power calculations were conducted focusing on the effectiveness aim using maternal self-report of depressive symptoms (measured by the Center for Epidemiologic Studies-Depression scale (CES-D)) and parenting practices (measured by the Parental Cognition and Conduct Towards the Infant Scale (PACOTIS)), assuming power = 80%, a two-tailed test with an alpha of 0.05. To do these power calculations, we used the PowerUp tool. We plan to recruit 300 participants for the trial, 150 participants per condition. Based on these numbers, we expect a minimal detectable effect size of 0.241. Because of the longitudinal nature of the study, we expect some attrition (~ 20%). Accounting for attrition, we can expect a minimal detectable effect size of 0.269. Based on prior research, we expect small to moderate effect sizes, which we will have the ability to detect. We believe clustering by group will be very small and thus do not take it into account in the power analysis. Doing so would lead to a small increase in the minimal detectable effect sizes (e.g., increasing from 0.241 to 0.284).

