### Missing data

Sample size and power calculations were completed under the assumption of 20% attrition for primary outcome analyses. Thus, while we anticipate missing data, we still expect adequate power to detect differences between study arms. We will examine rates of missing data for all variables and determine whether rates vary by participant characteristics, Judy Center program, or study arm. These analyses will indicate the extent to which missing data could bias results. We will attempt to collect data at each time point regardless of participants’ engagement in earlier data collection efforts. To minimize missing data due to loss to follow-up, we will devote considerable attention to promoting study retention. The planned mixed effects models are generally robust for unbalanced data across study time points. However, we plan to apply multiple imputation to test for bias introduced by missing data in sensitivity analyses; we will impute at least five datasets to generate an estimated average intervention effect.

We plan to perform all analyses using both the intent-to-treat (ITT) approach and a dose–response approach (treating dosage as a continuous variable of 0–10 sessions attended), adjusted for propensity scores. The dose–response approach will examine the relationship between number of MB-VG sessions attended (dosage) and outcomes, using propensity scores to match intervention participants to control-group participants with a similar propensity to take up a given level of intervention. This will reduce the influence of self-selection bias in intervention take up on the estimates of dosage effects. We plan to stratify analyses by whether participants are prenatal vs postpartum and whether participants are primiparous or multiparous.

Interim analysis will be performed to ensure safety. This analysis will focus on whether participating in the intervention has any significant iatrogenic effects. Individuals who score > 40 on the CES-D at any assessment timepoint will be flagged, since this level of symptomatology can be considered “very severe”; these participants will be contacted by the research team per procedures described below in the " Safety considerations and procedures" section. The safety analysis dataset will include those participants who had at least one session of the study intervention. No other formal planned interim analyses are planned.

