### Quantitative analysis

Descriptive statistics will summarize baseline characteristics overall and by study arm (i.e., usual family support services vs. MB-VG). As appropriate, mean ± standard deviation (or median [inner quartile range]) will be used in cases of skewed or non-normal empirical distributions and frequency (proportions) will summarize continuous and categorical data, respectively. Analyses will employ normal theory methodology as appropriate, and in cases of violations of assumptions, transformations, and/or nonparametric analyses may be utilized. Analyses will proceed at the participant level, and all hypothesis tests will assume a two-sided 5% level of significance. We will apply the Benjamini–Hochberg correction to control family-wise type I error rate to 5%. We plan to perform all analyses using both the intent-to-treat (ITT) approach and a dose–response approach, adjusted for propensity scores. Multilevel analysis, i.e., generalized mixed effects models, will estimate baseline and multivariate adjusted between-group differences, adjusted odds ratios (AORs), and 95% confidence intervals (CIs) using individual-level data but considering the hierarchical and clustered structure of data, with participants clustered by group (i.e., Judy Center). We believe clustering by group will be very small and thus do not take it into account in the power analysis. Doing so would lead to a small increase in the minimal detectable effect sizes (e.g., increasing from 0.241 to 0.284). Continuous outcomes will use a model that assumes normally distributed outcomes, and appropriate transformations of the data will be made to improve normality. Binary outcomes will be assessed using a logistic regression-based multilevel model.

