*Effectiveness outcomes*: Aim 1 will be tested by examining the coefficient of the treatment vs. control indicator in the random effects model. We will include random intercepts for group and instructors and will also investigate whether a random slope for group is appropriate for the intervention effect. Intervention group, covariates measured at pretest (especially the pretest measures of the outcome, as available), the Judy Center the participant was recruited from, and instructor characteristics will be included as fixed effects. Likelihood ratio tests (significance criterion, *p* < 0.05) will be used to simplify the models following a backward selection strategy. Although the primary analyses will consider each set of follow-up outcomes separately, controlling for pre-test measures in each analysis, we will also consider the use of longitudinal growth models to model the growth in knowledge over the three time points. Primary endpoint #1 is depressive symptoms, as measured by the Center for Epidemiologic Studies-Depression scale (CES-D). A total continuous score (0–60) is calculated for the CES-D. Primary endpoint #2 is depressive episodes as measured by the SCID. The SCID is used to assess the presence/absence of major depression, making it a binary outcome (yes/no). Primary endpoints #3 and #4 are parenting self-efficacy measured via the PACOTIS and parenting responsiveness measured via the MIRI and PCOS (used as a separate coding system when coding the DB-DOS observation assessment). A mean score is calculated for each of the PACOTIS and MIRI subscales. Secondary endpoint #1 is anxiety symptoms, measured via the GAD-7. A total continuous score is calculated for the GAD-7. Secondary endpoint #2 is perceived stress, measured via the PSS-10. A total continuous score is calculated for the PSS-10.

Covariates will be finalized in a Statistical Analysis Plan but based on our prior studies [80, 87] will include (1) whether participant is a first-time mother (e.g., current number of children = 0 at baseline; (2) education (at least some high school vs less than high school); (3) mental health service utilization (we will control for enrollment with a therapist for counseling at baseline and medication for depression at baseline).

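### The detectable effects of 0.241 and 0.269 are single-test figures at alpha 0.05; under the planned Benjamini–Hochberg correction, power at those effects is below 80% in any family of two or more tests

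*Protocol article*

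**What the plan says.** All references are to the protocol article.

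- **Statistical analysis.** Power is worked out for two outcomes, CES-D and PACOTIS, "assuming power = 80%, a two-tailed test with an alpha of 0.05". The sample is "We plan to recruit 300 participants for the trial, 150 participants per condition". The results are "Based on these numbers, we expect a minimal detectable effect size of 0.241" and "Accounting for attrition, we can expect a minimal detectable effect size of 0.269". The section adds that the small to moderate effects expected from earlier work will be detectable.
- **Missing data.** "Sample size and power calculations were completed under the assumption of 20% attrition for primary outcome analyses", and on that basis "we still expect adequate power to detect differences between study arms".
- **Quantitative analysis.** Tests are two-sided at 5%, and then: "We will apply the Benjamini–Hochberg correction to control family-wise type I error rate to 5" per cent. No family of tests is named, and no endpoint is exempted. The same section lists four primary endpoints (CES-D; SCID; PACOTIS; MIRI with PCOS) and says the primary analyses take each follow-up on its own.
- **Table 2.** CES-D is measured at three follow-ups, SCID, PACOTIS and MIRI at two, and PCOS at one. The abstract instead places PACOTIS and MIRI at all three follow-ups.

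**The concern.** The power figures allow each powered outcome the full 0.05. The analysis does not, unless that outcome is the only test in its family. Under Benjamini–Hochberg, a given p-value has to meet a cut-off between 0.05/m and 0.05, where m is the family size. The cut-off that applies depends on how many other tests in the family also give small p-values. A power figure computed at 0.05 is therefore an upper bound for the planned analysis.

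What is at stake is the article's claim to adequate power. The Background cites an effect size of −0.28 among all recipients in an earlier trial of the parent intervention. That lies just above 0.269 in magnitude, so a reader comparing the two would think the trial adequately powered for an effect of that order. The margin is gone or reversed once the correction is counted.

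**Working it through.** **Inputs.** Two-sided alpha 0.05, power 80%, N = 300 (150 per arm), 20% attrition (240 analysed), detectable effects 0.241 and 0.269: all from Statistical analysis and Missing data. Endpoints and visits: Quantitative analysis and Table 2.

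**1. Reproducing the plan's figures.** For two equal arms the detectable effect is (z₀.₉₇₅ + z₀.₈₀) × √(4(1 − R²)/N), with z₀.₉₇₅ + z₀.₈₀ = 1.960 + 0.842 = 2.802.

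- R² = 0: 2.802 × √(4/300) = 0.324 and 2.802 × √(4/240) = 0.362. These are not the printed figures.
- R² = 0.45: 0.240 and 0.268 (0.241 and 0.269 with the t distribution). These match.

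The value 0.45 is an assumption, solved back from 0.241; the article prints none and says only that baseline covariates are adjusted for, "especially the pretest measures of the outcome, as available". The attrition step also matches: 0.241 × √(300/240) = 0.269. So the printed figures fit one test at an unadjusted 0.05.

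The rest does not depend on R². Any effect with 80% power at 0.05 has a standardised mean (noncentrality) of 2.802.

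**2. Counting the tests.** Table 2 gives 3 (CES-D) + 2 (SCID) + 2 (PACOTIS) + 2 (MIRI) + 1 (PCOS) = 10. With the abstract's visits it is 3 + 3 + 3 + 2 = 11, or 12 with PCOS. If the family is one visit, Table 2 gives 1 test at 1 week (CES-D alone), 4 at 3 months and 5 at 6 months.

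**3. Strictest step, ten tests.** The cut-off is 0.05/10 = 0.005, z = 2.807. Power at the stated effect is Φ(2.802 − 2.807) ≈ 50%. The effect needed for 80% power grows by (2.807 + 0.842)/2.802 = 1.30, so 0.241 becomes about 0.31 and 0.269 becomes about 0.35.

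**4. The step-up procedure itself.** Benjamini–Hochberg at 0.05 was simulated with 100,000 runs and a common correlation of 0 to 0.7 between test statistics. Each real effect was set to the stated detectable size, so that it has 80% power at 0.05.

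| Family | Real effects | Power for one real effect | Effect needed for 80%, 240 analysed |
|---|---|---|---|
| 1 | 1 | 80% | 0.269 |
| 2 | 1 | about 72% | about 0.30 |
| 2 | 2 | 77–79% | not tabulated |
| 4 | 1 | 62–63% | about 0.32 |
| 4 | 4 | 75–78% | about 0.28–0.29 |
| 10 | 1 | about 50% | about 0.35 |
| 10 | 3 | 59–61% | about 0.32–0.33 |
| 10 | 10 | 73–77% | about 0.28–0.29 |
| 12 | 1 | 47–49% | about 0.36 |
| 12 | 12 | 73–77% | not tabulated |

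Before attrition, the ten-test range is 0.241 × 0.28/0.269 = 0.25 at best to 0.241 × 1.30 = 0.31 at worst.

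Every row with two or more tests is below 80%.

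**The case against.** Several counter-arguments carry weight.

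*The family is undefined, and ten is only a count.* This stands. By visit, under Table 2, CES-D at 1 week is a family of one and its 80% is untouched. That does not rescue the general statement: CES-D at 3 and 6 months falls in families of 4 and 5, and PACOTIS, which Table 2 does not schedule at 1 week, is never alone.

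*The 50% figure is the least favourable case.* This also stands. It needs a real effect on one test and none on the other nine, whereas the hypotheses expect benefit on symptoms, episodes and parenting. If everything works equally well, the loss is about 3 to 7 percentage points and the detectable effect moves only to 0.28–0.29. Equal strength throughout is itself optimistic, so the truth probably lies between. A reader might infer that the trial has 50% power or can detect only 0.35; the article does not support either as a general statement.

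*The article does not contain two rival decision rules.* Correct. A reader might infer that a CES-D result of p = 0.03 would pass under one section and fail under the other. The power section is a planning assumption; only the Quantitative analysis section governs significance.

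*The sample size was not shown to rest on the wrong alpha.* Correct. The article takes 300 as given and reports what that number can detect. Nor is the arithmetic wrong for the test it assumes.

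*The definition of the family may be left to the analysis plan.* That may be so, and its absence is not the point here. The article prints both a power claim and a correction, and the claim does not allow for the correction.

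**Conclusion.** The point holds in a limited form. The stated 80% power at 0.241 and 0.269 belongs to a single unadjusted test. For CES-D or PACOTIS in any corrected family of two or more, power at those effects is lower: from a few points below 80% if every endpoint responds equally, to about 50% if only one of ten does. After attrition the detectable effect is about 0.28–0.29 to 0.35 for ten tests.

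This rests on a normal approximation, a common correlation of 0 to 0.7, real effects of equal strength, and family sizes counted from the article rather than stated in it. The direction does not depend on these choices; the size does.

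Three related matters are not included in these figures: clustering, for which the article itself gives 0.284 instead of 0.241; the unprinted R²; and the fact that Benjamini–Hochberg controls the false discovery rate rather than the family-wise rate named as its aim. A family-wise method would cost more: Holm over ten tests gives about 50–61%.

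**What to change.** Name the family of tests to which the correction applies, and confirm the method. Then restate the power or detectable effect for CES-D and PACOTIS under that correction in the Statistical analysis and Missing data sections, as a range over how many endpoints carry an effect. Alternatively, say plainly that 0.241 and 0.269 are unadjusted single-test figures and print the adjusted ones beside them.

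The cost is a few sentences, a short simulation, and a somewhat less favourable stated figure. Sample size and design stay as they are.

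Testing one named CES-D contrast at 0.05 outside the family is an optional design choice, not the required correction. It would leave PACOTIS, which the power section also covers, under the correction, and it would rank the other primary endpoints below CES-D.
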